**Conclusion::**

The present research is designed to investigate efficacy and mechanism of traditional acupuncture therapy on ischemic PSD, also to explore the correlation between cerebra metabolic and serologic factors, and ischemic PSD. With this research, we are looking forward to find out an appropriate alternative nondrug therapy for PSD people to alleviate the adverse effects and drug dependence caused by antidepressants.

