## Introduction

1

Poststroke depression (PSD) is a serious and common complication of stroke.^[1]^ Reports revealed that the prevalence of PSD was from 30% to 65%.^[2,3]^ PSD has been associated negatively with survival, cost of medical care, and compliance with therapy including rehabilitation, functional outcome, resumption of social activities, and quality of life.^[4]^

At present, the treatment of PSD mostly applies selective serotonin reuptake inhibitors (SSRIs). A meta-analysis of randomized controlled trials for PSD has revealed that patients in the SSRIs group had make great improvement in depressive symptoms significantly compared with the placebo group.^[5]^ Several controlled studies have demonstrated that while some patients made improvement on depression scores significantly, others discontinued due to side effects.^[6,7]^ And SSRIs have slow onset speed about 3 to 4weeks.^[5]^ A trial suggested that the advantages of fluoxetine hydrochloride could not be demonstrated within the first 3 months compared with controlled treatment.^[8]^ On the contrary, the use of antidepressants might also increase the risk of interactions derived from various drugs, as most stroke patients concurrently take.^[9]^

Acupuncture is 1 of the main treatments of traditional Chinese medicine (TCM) which has been used for over 2000 years. Acupuncture is widely used in the treatment of PSD. A meta-analysis has demonstrated that the curative effect of acupuncture on PSD was superior to antidepressants among waitlist controls in improving both response and symptom severity.^[10]^ Another meta-analysis revealed that there is no difference in effective rate on comparison between the acupuncture group and western medicine group in treating PSD.^[11]^

In China, because of the good effect, more and more patients are willing to choose acupuncture for PSD. However, no sufficient clinical trial data and solid evidence could confirm whether acupuncture could yield certain efficiency in treating PSD and how acupuncture works. It is necessary to verify the effectiveness and mechanism of acupuncture from senior quality studies. Now, the evidence about acupuncture effect on treating PSD is inadequate and must apply further strictly design clinical studies.

The primary objectives of this study are to evaluate the efficacy and mechanism of acupuncture treatment and follow-up on PSD during 6 months.

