### Study design

2.1

This is a multicenter, central-randomized, single-blind, sham-controlled, noninferiority clinical trial. In all, 208 participants will be randomized into 2 groups at a ratio of 1:1. Participants in the treatment group will be treated with traditional acupuncture and placebo medicine. Participants in the control group will be treated with sham-acupoint acupuncture and medicine (fluoxetine hydrochloride tablets).

The whole study period is 25 weeks, including 1-week baseline observation, 12-week treatment, and 12-week follow-up. Patients will be evaluated with scales for clinical efficacy before and the 2nd, 4th, 8th, 12th week of treatment, and 24th week of follow-up, and monitored by proton magnetic resonance spectroscopy (^1^H-MRS) and serum for acupuncture mechanisms before and the 12th week of treatment (Fig. 1).

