### Randomization and blinding

2.12

After recruitment, the Central Randomization System performed by the China Academy of Chinese Medical Sciences (CACMS) would be used to randomize patients who meet the eligibility criteria into 2 groups at a ratio of 1:1. Every center will compete for the random numbers from random sequence generated by the Central Randomization System. Each subject will be registered with a unique ID. After the clinical screening and getting the informed consent forms, subjects will be assigned to experimental group (verum acupuncture + placebo pills) and control group (sham-acupoints acupuncture + fluoxetine) randomly. Each subject will receive the similar the number of acupoints and medications, as well as the stimulating amount of needling. Both groups will be in the package with the same looking and similar inner feeling, whereas all subjects will not be aware of the grouping.

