#### Primary outcomes

2.13.1

We will use univariate repetitive measurement deviation analysis with HAMD-17 and SDS scores before and the 2nd, 4th, 8th, 12th week of treatment, and 24th week of follow-up as the outcomes. A significant effect of group indicates that the HAMD-17 and SDS scores are different between groups after interventions.

The diversity of Cho, NAA, MI, Glx, Cr, Cho/Cr, Cho/NAA, and Cr/NAA will be compared with 2-sample *t* tests or Wilcoxon rank-sum test with their concentrations or ratios before and the 12th week of treatment as the outcome variables. Similar analysis approach will be used for the levels of 5-HT, NE, DA, BDNF, IL-4, IL-6, IL-10, IL-18, IL-1β, and TNF-α in serum.

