## Discussion

3

Poststroke depression is a secondary neuropsychiatry disease, which is now considered its pathogenesis involving endogenous factors like neurochemical substances and inflammatory cytokines, and also exogenous factors like sex, age, marriage, social environment, education, life stress, and so on by reference to the primary depression.^[26]^ It is still unknown whether the pathogenesis is with particularity for PSD itself. Apart from this, the PSD diagnosis is confusion. The CCMD-III, ICD-10, and DSM-IV are the most commonly used in China.^[27]^ However, there was no clear diagnostic criterion for PSD above. DSM-IV categorizes PSD as “Mood disorder due to a general medical condition (ie, stroke),” with the specificities of depressive features, major depressive-like episodes, manic features, or mixed features. Refer to the diagnostic criteria of depressive episode in CCMD-III, ischemic stroke patients who were in depressed mood will be diagnosed with PSD. Therefore, according to patient symptoms combined with rating scale scores, we hope to obtain high-quality research data from this multicenter clinical trial that could provide reliable basis to future related study.

Fluoxetine hydrochloride, which is chosen as a standard drug therapy in this study, has been found to be effective and safe in PSD.^[28,29]^ A large number of ischemic stroke patients are recommended to take clopidogrel to prevent thrombosis.^[30]^ However, antidepressants might also increase the risk of drug-drug interactions. For example, SSRIs like fluoxetine and fluvoxamine are always avoided in ischemic heart disease patients who are receiving clopidogrel.^[31]^ Also, other studies have found that fluoxetine may potentially diminish the efficacy of clopidogrel.^[32]^ Moreover, the US Food and Drug Administration (FDA) reminded the public to avoid fluoxetine hydrochloride combination with clopidogrel because of the reasons above,^[33]^ especially for stroke patients. Hence, patients diagnosed with depression after ischemic stroke who were useing clopidogrel would not be recommended to take fluoxetine.^[34]^ For this, acupuncture on PSD may be a promising alternative therapy.

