Acupuncture has been widely used and received in clinical practice in China.^[35]^ Patients in China are usually familiar with acupuncture, and expect to receive acupuncture treatments when they participate in this kind trial. Apart from this, because acupuncture is often regarded as an invasive operation,^[36]^ it is difficult to design a nonpenetrating sham acupuncture, which does not produce any physiological effects,^[37]^ and would not be experienced and recognized by patients at home. However, to improve subject compliance and achieve blinding, sham acupuncture will be necessary in the control group, whereas placebo pills will be adopted in experimental group in a high-quality RCT. So, in this study, sham acupuncture and placebo pills are applied simultaneously to eliminate the placebo effect. We choose needling at blunt acupoints as sham acupuncture without effect on depression, based on literatures^[18]^ and clinical experience.

Although studies have showed the efficacy of acupuncture for PSD,^[38,39]^ multicenter and large-sample RCTs are still lacking, and also the relevant mechanism research, which would be helpful to provide high-quality evidence for evaluation of acupuncture on PSD. Our protocol was designed through an extensive discussion by reference to several previous related studies.^[40–42]^ We try our best to attempt to minimize the biases that may influence study results. Finally, we intend to demonstrate the hypothesis that acupuncture as an alternative may be validated for PSD.

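### The planned marker tests compare acupuncture with fluoxetine plus sham needling, so they cannot show whether acupuncture itself changes a marker, and no stated analysis serves the marker–depression correlation aim

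*Protocol article*

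**What the plan says.** The Introduction of the protocol article sets the aim: "The primary objectives of this study are to evaluate the efficacy and mechanism of acupuncture treatment and follow-up on PSD during 6 months". The Abstract's conclusion adds a second aim: "also to explore the correlation between cerebra metabolic and serologic factors, and ischemic PSD".

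Section 2.9 lists the brain metabolites and serum factors among the primary outcomes, and the article schedules them at baseline and week 12. Section 2.13.1 gives the test for the metabolites as a two-sample t test or "Wilcoxon rank-sum test with their concentrations or ratios before and the 12th week of treatment as the outcome variables", and applies a similar approach to the serum factors.

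The groups compared are, in section 2.12, "experimental group (verum acupuncture + placebo pills) and control group (sham-acupoints acupuncture + fluoxetine) randomly". Section 2.1 calls the study a "multicenter, central-randomized, single-blind, sham-controlled, noninferiority clinical trial", and the Discussion says of fluoxetine that it "has been found to be effective and safe in PSD".

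Section 2.13 also plans descriptive statistics by group and time. Sections 2.13 to 2.13.3 name no paired test, correlation or regression for the markers.

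**The concern.** The question is how acupuncture works, but the contrast tested is acupuncture minus fluoxetine-with-sham-needling. Three different situations give the same expected result of no difference: both treatments move the marker alike, neither moves it, or both arms share the same spontaneous change after stroke. If a difference does appear, it may be an effect of acupuncture, an effect of fluoxetine, or a mix.

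The correlation aim needs an analysis that links a patient's marker to that patient's depression score, and a comparison of arms does not do this. Every participant has PSD under the inclusion criteria, so PSD cannot be contrasted with stroke without depression. Only a correlation within PSD is possible.

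At stake is the reading of one of the two primary objectives. A null result could be reported as a shared mechanism, or as no effect of acupuncture, and the test supports neither. The efficacy analysis of HAMD-17 is not affected.

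**Working it through.** **1. The plan's own figure.** The article gives no sample size or effect for the markers. Its only figure is for HAMD-17 (section 2.11): at least 84 per group, 104 after 20% dropout, from changes of 10.49 (SD 4.55) and 10.24 (SD 4.46).
- Pooled SD = √((4.55² + 4.46²)/2) = 4.505.
- The article does not state the margin, so 84 cannot be reproduced from its inputs. It fits an assumed margin of about 2.0 points: with one-sided 0.025 and a true difference of 0.25 in favour of acupuncture, n = 2 × 4.505² × (1.960 + 1.282)² / 2.25² ≈ 84.3, so 85.
- Dropout: 84/0.8 = 105, against the stated 104.

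Nothing below rests on this figure except the use of 84 evaluable patients per arm.

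**2. The planned between-arm test.** Assumptions: marker change is normal with equal SD in both arms, effects are in SDs of change, the level is two-sided 0.05 (the article does not state sidedness), and n = 84 per arm. Effect sizes are assumed because the documents give none. Power comes from the noncentral t distribution, with noncentrality (d_acupuncture − d_fluoxetine) × √(n/2) between arms and d_acupuncture × √n within the acupuncture arm.

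| Shift, acupuncture arm | Shift, fluoxetine arm | Between-arm test significant | Within-acupuncture test significant |
|---|---|---|---|
| 0 | 0 | 5.0% | 5.0% |
| 0.5 | 0.5 | 5.0% | 99.5% |
| 0.8 | 0.8 | 5.0% | 100% |
| 0.5 | 0.4 | 9.9% | 99.5% |
| 0.5 | 0.25 | 36% | 99.5% |
| 0.8 | 0.4 | 73% | 100% |
| 0.5 | 0 | 90% | 99.5% |
| 0 | 0.5 | 90% | 5.0% |

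For the row 0.5 against 0, the noncentrality is 0.5 × √42 = 3.24. Simulation with 20,000 trials agrees: 4.9% at 0.5/0.5, 5.0% at 0.8/0.8, 4.9% at 0/0 and 89.7% at 0.5/0.

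The first three rows cannot be told apart by the planned test. The last two have the same rejection rate, although in one only acupuncture acts and in the other only fluoxetine does. The sign of the difference does not settle this either, because a drop under one treatment looks like a rise under the other.

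**3. Multiplicity.** Section 2.9 lists 8 metabolite measures and 10 serum factors, 18 before brain regions are counted. At an unadjusted 0.05, the chance of at least one false difference is 1 − 0.95¹⁸ = 60% if the tests were independent.

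**4. What a correlation analysis could detect.** By Fisher z, detectable r = tanh((z_α + z_power)/√(n − 3)) at 80% power, with 2 × 84 = 168 patients pooled or 84 in one arm.
- One test, two-sided 5%: tanh((1.960 + 0.842)/√165) ≈ 0.21 pooled; tanh(2.802/√81) ≈ 0.30 per arm.
- Bonferroni over 18 (0.05/18 = 0.0028): tanh((2.99 + 0.842)/√165) ≈ 0.29 pooled; tanh(3.83/9) ≈ 0.40 per arm.
- Difference between arms in correlation, one test: tanh(2.802 × √(2/81)) ≈ 0.41 in one arm against 0 in the other.

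**The case against.** **Both treatments working does not force a null.** A reader might infer that if acupuncture and fluoxetine both relieve depression, the marker test must show no difference. The documents do not support that. Similar HAMD-17 change (10.49 and 10.24) does not imply similar change in any marker. The treatments may act through different markers, and the planned test could then detect a difference (up to 90% in the range above). The null is expected only where both arms move the same marker by about the same amount. The 5% figure holds for any test of two equal means. It shows that the situations cannot be told apart, and does not predict what this trial will find.

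**The between-arm test is legitimate.** It is the only randomised contrast available for the markers, and it validly asks whether the two treatments differ in marker profile. Within-arm values are to be described by group and time, so they are not ignored, only left without inference. Section 2.13 also mentions repeated-measures analysis for primary outcomes in general, although 2.13.1 names only two-sample tests for the markers. All of this stands, and it is why the comparison should be kept.

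**The correlation may be specified elsewhere.** It is worded as exploratory, appears in the Abstract and not among the stated primary objectives, and its method could sit in an analysis plan that is not shown. This is therefore the weaker part of the point. The mismatch between the mechanism objective and the test the article does fix does not depend on it.

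**The sham is not shown to be active on the markers.** The Discussion says that "it is difficult to design a nonpenetrating sham acupuncture, which does not produce any physiological effects", from which a reader might infer that the chosen needling moves the markers. The article does not say so, and it describes the chosen points as having no effect on depression.

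**Added analyses do not cure the design.** This stands. With no sham-plus-placebo arm, within-arm change mixes treatment, natural recovery and regression to the mean.

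**Conclusion.** The point holds in a limited form. The tests fixed in section 2.13.1 estimate acupuncture against fluoxetine plus sham needling. They cannot by themselves show that acupuncture changes a marker. A non-significant result would not distinguish a shared effect from no effect, and it would not show similarity, because no equivalence margin is set for the markers. A significant result could come from either treatment. No analysis in the article serves the correlation aim.

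The size depends on how alike the two treatments are on a given marker. Rejection runs from 5.0% with equal shifts to 90% for 0.5 SD against none, with 84 per arm and assumed effects. The consequence is a limit on the mechanism conclusions, which can be partly relieved with data already planned. It does not make the marker data useless, and the randomised comparison is not wrong for the narrower question it answers.

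**What to change.** In section 2.13.1:

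- Keep the randomised between-arm comparison, preferably of the week-12 marker adjusted for its baseline value. State that it addresses only acupuncture versus fluoxetine plus sham needling, and that a non-significant result is not to be read as a shared mechanism or as no effect.
- Add within-arm marker change from baseline to week 12 with confidence intervals. State that, without a sham-plus-placebo arm, this change cannot be separated from natural recovery.
- Add a regression of HAMD-17 change on marker change over the same 12 weeks, adjusted for baseline HAMD-17, baseline marker and arm. Do not adjust for NIHSS change: it arises after randomisation and treatment may affect it. Label any marker-by-arm term exploratory, since its power is low.
- Label the two added analyses associational, and acknowledge multiplicity across the 18 markers, with the detectable correlations above (0.21 and 0.30 for one test, 0.29 and 0.40 with Bonferroni).

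Reword the aim in the Abstract as correlation with depression severity among patients with PSD over 12 weeks. The markers are not scheduled at week 24, and no stroke patients without depression are enrolled.

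The cost is analysis text and some extra computation. No new data are needed, because HAMD-17 and the markers are already scheduled at both time points. The price is a weaker mechanism claim: association within PSD, not cause.

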#### Secondary outcomes

2.13.2

Continuous outcome variables including NIHSS scores, MBI scores, diagnosis and evaluation criteria of TCM for stroke (try out) scores and CGI scores before and the 2nd, 4th, 8th, 12th week of treatment, and 24th week of follow-up will be analyzed with univariate repetitive measurement deviation analysis. Categorical outcome variables in the patients’ diary and chi-square test will be used for comparison between groups.

#### Safety evaluation

2.13.3

Adverse effects will be evaluated by TESS scores with univariate repetitive measurement deviation analysis between groups at different time. Adverse events will be analyzed as a multiply variable. The number and percentage of patients with AE will be calculated and compared using chi-square test.

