### Adverse events observation

2.8

It could be that patients with subcutaneous bleeding or hematoma, needle sickness, and pain around acupionts at needling are more likely related to acupuncture. Sickness, vomiting, diarrhea, headache, anxiety, insomnia, drowsiness, fatigue, sweating, tremors, and skin rash occur in patients are probably connected to drugs. With the Treatment Emergent Symptom Scale (TESS) and patients’ diary, all adverse events are to be recorded and measured during treatment and the follow-up period. Serious adverse events should be reported to the principal investigator immediately. All details will be documented, appropriate medical care will be given at once.

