### Secondary outcomes

2.10

National Institute of Health Stroke Scale (NIHSS)^[20]^ scores for neurological deficit, Modified Barthel Index (MBI)^[21]^ scores for activities of daily living (ADL), TESS^[22]^ scores for side effects of treatments, diagnosis and evaluation criteria of TCM for stroke (try out)^[23]^ scores for curative effects of stroke, and clinical global impression (CGI)^[24]^ scores for synthesize effect before and the 2nd, 4th, 8th, 12th week of treatment, and 24th week of follow-up. Patients’ diary for tracking their mood, sleep, diet, medications, adverse events, and others during the research was maintained. All the dropouts and causes will be documented in case report form (CRF).

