### Estimation of sample size

2.11

Based on the previous pilot study,^[25]^ the mean change in HAMD-17 before and after treatment was used as the indicator for the efficacy evaluation in the calculation of the sample size. Results from our previous studies showed that the mean HAMD-17 scores change was 10.49 ± 4.55 after acupuncture treatment and 10.24 ± 4.46 after fluoxetine treatment. Thus, we performed a noninferiority test to calculate the appropriate trial sample size with 90% power, beta of 0.1, alpha of 0.05. The results showed that a clinically important difference can be detected by a sample size of at least 84 in each group. This number was then increased to 104 per group to allow a predicted 20% dropout rate. We will plan to enroll in all 208 participants in this study.

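### The TESS side-effect comparison does not use the pre-treatment rating as a reference, so under the protocol's own reading of its method a real between-arm difference is diluted to about 83% or 67%

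*Protocol article*

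**What the plan says.** Section 2.10 of the protocol article makes TESS a secondary outcome, as "scores for side effects of treatments". The rating times close the list that contains TESS: "scores for synthesize effect before and the 2nd, 4th, 8th, 12th week of treatment, and 24th week of follow-up". I read them as applying to every scale in that list, which gives six ratings. Section 2.1 sets 12 weeks of treatment and 12 of follow-up, so the week-24 rating falls 12 weeks after treatment ends.

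Section 2.13.3 gives two safety analyses. The first is: "Adverse effects will be evaluated by TESS scores with univariate repetitive measurement deviation analysis between groups at different time". The second is: "The number and percentage of patients with AE will be calculated and compared using chi-square test". Neither has a rule for using the pre-treatment rating.

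Section 2.13.1 applies the same repeated-measures method to HAMD-17 and SDS. It lists the pre-treatment score among the outcomes and reads the result thus: "A significant effect of group indicates that the HAMD-17 and SDS scores are different between groups after interventions".

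Section 2.8 says that, with TESS and the patient diary, "all adverse events are to be recorded and measured during treatment and the follow-up period". It also describes the events expected from the drug: "Sickness, vomiting, diarrhea, headache, anxiety, insomnia, drowsiness, fatigue, sweating, tremors, and skin rash occur in patients are probably connected to drugs".

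**The concern.** A symptom rated before the first session or tablet cannot be a side effect of treatment. Randomised arms do not differ on average at that rating, so including it as one more outcome adds no information about harm and pulls the group effect towards zero. The week-24 rating does the same if side effects stop when treatment stops.

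The score also does not separate new complaints from old ones. Anxiety, insomnia, drowsiness and fatigue are on the section 2.8 list of drug-type symptoms, but they can also belong to the depression for which patients are enrolled. A patient who enters with insomnia and keeps it scores the same on that item as one who develops it on treatment.

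Efficacy and mechanism are the primary objectives, but the article's conclusion hopes that acupuncture will spare patients the adverse effects of antidepressants. A diluted tolerability comparison weakens the evidence on that hope. It could also miss a real difference in either direction.

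**Working it through.** The document gives no TESS standard deviation, effect size or power, so there is no stated figure to reproduce. The steps below separate what follows from the visit schedule from what needs assumptions.

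**Step 1: dilution (schedule only).** Let the between-arm TESS difference be *h* at each visit where harm is present and 0 elsewhere. The group effect over six ratings is *h* × (visits with harm)/6.

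- Harm at weeks 2, 4, 8, 12 and 24: 5/6 = 83% of *h*.
- Harm at weeks 2, 4, 8 and 12 only: 4/6 = 67% of *h*.

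**Step 2: effect on power (illustrative).** From section 2.11: 84 evaluable patients per arm. From section 2.13: significance at 0.05, taken here as two-sided. Assumed: *h* = 0.4 SD, and equal correlation ρ between visits, from 0.3 to 0.7.

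- Variance of the mean of *m* ratings, in SD units: (1 + (*m* − 1)ρ)/*m*.
- Variance of the mean of the four on-treatment ratings, adjusted for baseline: (1 + 3ρ)/4 − ρ².
- SE of the arm difference: √(2/84 × variance).
- Power: Φ(effect/SE − 1.96).

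Worked at ρ = 0.5, with harm at weeks 2 to 12 only:

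- Six raw ratings: variance 3.5/6 = 0.583, SE 0.118, effect 0.4 × 4/6 = 0.267, power 0.62.
- Four on-treatment ratings, unadjusted: variance 2.5/4 = 0.625, SE 0.122, effect 0.4, power 0.91.
- Four on-treatment ratings, adjusted for baseline: variance 0.625 − 0.25 = 0.375, SE 0.094, effect 0.4, power 0.99.

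| Analysis | ρ = 0.3 | ρ = 0.5 | ρ = 0.7 |
|---|---|---|---|
| Six raw ratings, harm lasting to week 24 | 0.92 | 0.81 | 0.70 |
| Six raw ratings, harm at weeks 2–12 only | 0.76 | 0.62 | 0.51 |
| Weeks 2–12, unadjusted (either pattern) | 0.96 | 0.91 | 0.84 |
| Weeks 2–12, adjusted for baseline (either pattern) | 0.99 | 0.99 | 1.00 |

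The ordering does not depend on *h*. At ρ = 0.5 with harm at weeks 2 to 12 only, six raw ratings against the adjusted analysis give 0.40 against 0.89 for *h* = 0.3, and 0.81 against 1.00 for *h* = 0.5.

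**Step 3: mood.** Let *H* be the net harm of fluoxetine over acupuncture on the score, and M_F and M_A the fall in overlapping symptoms from better mood on fluoxetine and on acupuncture. The expected TESS difference, fluoxetine minus acupuncture, is *H* − (M_F − M_A). Equal improvement cancels. Section 2.11 reports that "the mean HAMD-17 scores change was 10.49 ± 4.55 after acupuncture treatment and 10.24 ± 4.46 after fluoxetine treatment". The gap is 0.25 points. Against a pooled SD of √((4.55² + 4.46²)/2) = 4.505, that is about 0.06 SD of HAMD-17 change. Little net distortion from mood is therefore expected on the protocol's own figures for total change.

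Timing is less certain. The Introduction gives SSRIs an onset of about three to four weeks, and TESS is rated at week 2, so M_F and M_A could differ early even if they end up alike.

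**The case against.** The strongest reply is that the score analysis does not stand alone. The adverse-event comparison in the same section counts patients with events, and section 2.8 records events only during treatment and follow-up. New nausea or tremor could be counted there whatever the total score does. This stands in part. The comparison covers new events, but it draws on TESS and the diary with no rule to separate a new complaint from a continuing one.

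Second, section 2.13.3 does not itself say that the pre-treatment score enters the TESS model. That is inferred from the rating schedule in 2.10 and the treatment of the depression scales in 2.13.1. The wording could mean a group-by-time test, which uses the pre-treatment rating as a reference and is not diluted in the same way. This stands, and the dilution figures are conditional on the 2.13.1 reading.

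Third, baseline handling and treatment-emergent definitions are often left to an analysis plan, which is not shown. That is fair for a missing detail. Here, however, the article names an analysis and, for the same method, how to read it. Followed that way, it gives a diluted and less precise answer.

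Three stronger readings are tempting, and the document does not support them:

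- A reader might infer that improving mood will hide new harm. One patient's total can indeed stay flat while new symptoms replace old ones, but the planned comparison is between randomised arms, where shared improvement cancels.
- A reader might take the four overlapping symptoms among the eleven in section 2.8 as a measure of how much of TESS is contaminated. The TESS items are not listed, so no such share can be given.
- A reader might infer that sorting symptoms by presumed source, needle or drug, biases the comparison. The wording in 2.8 is tentative, and no planned comparison uses the sorting.

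**Conclusion.** The point holds as one of analysis choice and is worth correcting. Read as section 2.13.1 reads the same method, the TESS analysis shrinks a true between-arm difference to 83%, or to 67% if harm stops with treatment. These fractions follow from the visit schedule, given a constant harm at the affected visits and inclusion of all six ratings.

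The power figures (0.62 against about 0.99 in the central case with harm confined to weeks 2 to 12) also rest on an assumed harm of 0.4 SD, equal correlation between visits and 84 evaluable patients per arm. They show the direction and rough size of the loss and do not predict the trial's power.

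Separately, pre-existing complaints count the same as new ones in the score, and the adverse-event comparison only partly repairs this. Bias from mood needs unequal or differently timed improvement between the arms. The protocol's pilot figures do not point to unequal total improvement, and they leave the timing open.

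**What to change.** In section 2.13.3:

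1. Use the pre-treatment TESS only as a reference. Compare the week 2, 4, 8 and 12 scores between arms, adjusted for the pre-treatment score.
2. In the comparison of patients with adverse events, count a TESS symptom as a side effect only if it was absent before treatment or is rated worse than its own pre-treatment rating.
3. Report week 24 separately as an off-treatment assessment.

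The pre-treatment TESS is already collected, so no extra visits or data are needed. The cost is a few sentences in the plan and slightly more analysis work. Proportions of patients carry less information than a score, and keeping the baseline-adjusted score analysis beside them offsets that loss.
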